### Procedures

#### Study schedule

The items to be measured at each visit are presented in Table 1.

**Table 1 Tab1:** Schedule of enrollment, intervention, and assessment

	Screening Visit 1 (day −5 to − 2)	Post allocation						Close-out
		Visit 2 (day 0)	Visit 3 (week 1)	Visit 4 (week 2)	Visit 5 (week 3)	Visit 6 (week 4)	Visit 7 (week 8)	Visit 8 (week 12)
Informed consent	X							
Inclusion/exclusion criteria	X							
Randomization		X						
Intervention		X	X	X	X	X	X	X
Vital signs	X	X	X	X	X	X	X	X
Body measurement^a^	X	X	X	X	X	X	X	X
Basic information^b^	X							
Heart function classification	X							
Medical history^c^	X							
General physical examination	X							X
HRV	X							X
RPP	X			X			X	X
Self-rating Anxiety Scale	X							X
Laboratory tests^d^	X			X				X
Heart Doppler ultrasound indexes^e^	X							
Compliance monitoring				X				
Adverse event monitoring			X	X	X	X	X	X

^a^ Height and weight, but only weight for visit 2 and follow-up

^b^ Age job, education level, dietary habit, smoking habits, drinking habits, etc.

^c^ Including general medical history and family history of coronary heart disease

^d^ Including triglyceride, total cholesterol, high-density lipoprotein, low-density lipoprotein, and fasting plasma glucose

^e^ Including left ventricular ejection fraction, left atrium dimension, left ventricular end-diastolic dimension, left ventricular end-diastolic volume, left ventricular end-systolic volume, etc.

#### Baseline assessment

After the screening visit, if a participant fulfills the inclusion criteria and has signed the informed consent form, he will be assigned to the baseline assessment. The baseline assessment takes place at visit 1. Baseline assessment includes patients’ basic information (such as age, gender, marital status, occupation, level of education, dietary habits, income, family history, co-morbidities, number of diseased coronary vessels, previous myocardial infarction, history of stent implantation, etc.), heart function classification, physical anthropometry indexes (height, body weight, blood pressure, heart rate, BMI, RPP, and HRV), heart Doppler ultrasound indexes (left ventricular ejection fraction, left atrium dimension, left ventricular end-diastolic dimension, left ventricular end-diastolic volume, left ventricular end-systolic volume, etc.), testing items (triglyceride [TG], total cholesterol [TC], HDL-C, LDL-C, and fasting plasma glucose), questionnaires (SAS).

#### Intervention group

After enrollment, the intervention group was given the following measures on the basis of receiving the routine health education. Each patient in the intervention group will be assigned a health management document and have a follow-up timetable.
Development and distribution of manuals: the Chinese Biomedical Literature Database (CBM) will be searched using the Chinese search terms “health management,” “diet,” “exercise,” “heart rate,” and “blood pressure” and the Cochrane Library, JBI, and Medline will be searched using the corresponding English search terms. After two rounds of expert consultation, the health education manual for patients with SCAD will be constructed and distributed to each patient in the intervention group upon discharge.One-to-one telephone follow-up or home visit: the patient will be followed up after discharge. Follow-up time is 3 months for a total of 12 weeks (once a week in the first month and once a month after that until 3 months). Two follow-up methods will be adopted: telephone and home visit. The telephone follow-ups last about 5–10 min each. Holding time could be extended if there is any problem consultation. Home visits will be scheduled with patients in advance and will last about 30–60 min each. During the follow-up, we will address the patient’s doubts and evaluate the effectiveness of the intervention.VBE guidance: before VBE, patients should rest for 5 min and then do it in a well-ventilated room with appropriate temperature. The researchers help patients take comfortable positions (supine, repose, and standing are all acceptable, sitting is recommended), straighten their head and back, and relax their whole body. The researchers instruct patients to extend the duration of exhalation and inhalation, and to minimize the breathing rate to 6 breaths/min. Participants practice silently counting from 1001 to 1004 on the inhale phase and 1001–1006 on the exhale phase to control the breathing rhythm and slow down the frequency. Participants are also encouraged to use abdominal breathing (a bulge in the abdomen when inhaling and a depression when exhaling) to deepen breathing depth and reduce breathing rate. Practice time: the total time per day is more than 30 min [25], which can be delivered in batches, but for at least 10 min at a time and at least five times a week [12].

Attention: The participants should breathe in and out of the nose during the whole process. The intensity of the exercise should not cause breath-holding or any physical discomfort. If discomfort occurs, participants may rest for a while and continue the exercise if no discomfort is present. For the first 3 days of the study, participants are asked to complete exercises in an outpatient classroom and the researchers will assess whether the exercises are correct or if they need to correct wrong breathing patterns.
4.Exercise log: each participant is given an exercise log and asked to record the number and time of exercise every day. These data can be used to assess intervention compliance.5.Network support: the research group will make self-breathing exercise material or video and transmit it to each participant through the network, so that participants could browse at any time.

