### Objectives

The main goal of this RCT is to evaluate the effect of VBE on HRV and myocardial oxygen consumption in patients with SCAD. First, HRV will be measured using the generally recommended time-domain analysis in 24 h; second, since RPP are highly correlated with myocardial oxygen consumption, it will be used as an indicator to estimate oxygen consumption of the myocardium.

The second objective is to explore the effect of VBE on reducing anxiety in patients with SCAD. Anxiety will be measured using the Self-rating Anxiety Scale (SAS) developed by Zung [29] in 1971.

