## Methods

### Study design and setting

This is a 6-month, single-blind RCT that will be conducted in the First Affiliated Hospital of Soochow University. Written informed consent will be obtained from each individual by the researcher after the individual has received a sufficient explanation and period of time in which to make a thoughtful decision. All the patients will be randomized 1:1 into the VBE-based clinical trial monitoring group (n = 70) or the Routine follow-up group (n = 70). The VBE-based clinical trial monitoring group is given VBE training on the basis of conventional treatment and health education, while the control group received conventional health education and follow-up. The two groups will be followed up for 3 months (Step 1). Considering the ethics and the fairness of the resources, we refer to the step-wedge design [30] and give the control group the same VBE guidance and follow up for another 3 months (Step 2) (see the flow diagram in Fig. 2). The Cardiovascular Medicine Department of the First Affiliated Hospital of Soochow University is currently the largest cardiovascular disease diagnosis and treatment center in South Jiangsu Province, China. The department carried out the first PTCA surgery in China in 1983. It has 180 beds, including 20 fully equipped Coronary Care Unit (CCU) beds, four cardiac catheterization rooms with advanced equipment, as well as a cardiac supersonic room and cardiac function room, and 1500 m^2^ cardiovascular laboratory. Annually, an average of 100,000 outpatients, 5000 open-heart surgery candidates, and 400 emergency operations are treated in the department.

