#### Control group

Routine education: on the first day after enrollment, researchers explain relevant knowledge of SCAD to patients, including risk factors, diet, weight control, physical exercise, blood pressure, lipid management, etc.Telephone follow-up: once per month for 3 months, each call lasting about 5–10 min, receiving telephone counseling from patients.Post-intervention: the control group will be given the same intervention measures 3 months later, and the effects of the control group will be compared before and after the intervention.

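### Only the VBE arm also receives a general education manual and denser follow-up, so a difference between arms cannot be attributed to breathing exercises alone, which is the stated aim

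*Protocol article*

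**What the plan says.** **The question.** Under Objectives: "The main goal of this RCT is to evaluate the effect of VBE on HRV and myocardial oxygen consumption in patients with SCAD".

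**The arms in summary.** Under Study design and setting, the intervention arm "is given VBE training on the basis of conventional treatment and health education, while the control group received conventional health education and follow-up". The Abstract describes the arms in the same way. On this description VBE is the only thing added.

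**The arms in detail.** The Intervention group section says that "the intervention group was given the following measures on the basis of receiving the routine health education" and then lists several measures. Besides VBE guidance, log and video, these are:

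- a personal health management document with a follow-up timetable;
- a SCAD education manual, for which the literature "will be searched using the Chinese search terms “health management,” “diet,” “exercise,” “heart rate,” and “blood pressure"; it "will be constructed and distributed to each patient in the intervention group upon discharge";
- one-to-one follow-up, "once a week in the first month and once a month after that until 3 months". On its form: "Two follow-up methods will be adopted: telephone and home visit". Calls take 5–10 min and home visits 30–60 min.

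The Control group section lists one oral education session on the first day after enrolment and this follow-up: "Telephone follow-up: once per month for 3 months, each call lasting about 5–10 min". It mentions no manual, management document or home visit. After 3 months, controls receive the same measures as the intervention arm (Step 2).

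**The concern.** The randomised contrast is wider than the question. General health education and more frequent professional contact differ between the arms along with the breathing exercises, and no analysis can separate components that are always given together to one arm.

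These components bear on the outcomes. The Background defines the rate-pressure product (RPP), a primary outcome, as heart rate times systolic pressure; the manual's search terms name both heart rate and blood pressure. Diet and exercise advice bears on the lipid, weight and BMI outcomes, and personal contact on self-rated anxiety. For 24-h heart rate variability (HRV), the other primary outcome, the documents do not indicate whether a manual or extra contact would change it.

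At stake is the conclusion. A positive result would be reported as an effect of breathing exercises when the design supports only an effect of the package. The limitations in the Discussion do not mention this.

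**Working it through.** The plan gives no figure on this point to reproduce. The check compares the components of the two arms and counts scheduled contacts.

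**Components (Intervention group and Control group sections)**

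| Component | Intervention arm | Control arm | Part of VBE itself? |
|---|---|---|---|
| Routine education | yes | yes, oral, day 1 | no, but matched |
| Breathing guidance, 3 supervised classroom days, log, video | yes | no | yes |
| General SCAD manual | every patient | not listed | no |
| Health management document | every patient | not listed | no |
| Follow-up contacts | weekly in month 1, then monthly | monthly | partly, as support |
| Home visits of 30–60 min | possible, number not given | not listed | partly, as support |

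The manual is the clearest unmatched item that can be separated from VBE: its search topics are general, and breathing training does not depend on it.

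**Contact count from the text sections**

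- Intervention arm: 4 weekly + 2 monthly = 6 contacts. Control arm: 3 monthly calls.
- If all are calls: 6 × 5 to 6 × 10 = 30–60 min, against 3 × 5 to 3 × 10 = 15–30 min.
- Each home visit replaces a 5–10 min call with 30–60 min. The split is not stated, so no total including home visits can be given.

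**Table 1 and Primary outcome measure**

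Table 1 has one schedule for all patients, with visits at weeks 1, 2, 3, 4, 8 and 12. That is also six, and it matches the intervention arm's follow-up. RPP is due at visits 4, 7 and 8 (weeks 2, 8 and 12) and must be measured in the outpatient classroom after 15 min seated. Two readings are possible:

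1. *Controls have only the monthly calls.* The contact gap is 6 to 3. No control contact falls at week 2, and a call cannot deliver an RPP measurement.
2. *Controls attend every Table 1 visit.* The gap in number of contacts largely closes, but the Control group section does not describe this schedule. The manual, the management document and the home visits remain unmatched.

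The attribution problem holds under both readings; only the size of the contact gap depends on which one is meant.

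**Step 2.** Controls receive the whole set of measures and are compared with themselves before and after. That contrast again includes manual, follow-up and VBE together, and has no concurrent control.

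**The case against.** **An add-on comparison with usual care is legitimate.** VBE is practised unsupervised at home, and the follow-up is there to answer questions and see how the intervention is working. An attention-matched control is a choice, not a requirement. This stands for the denser follow-up and, in part, for the home visits. It does not cover a general health manual.

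**The topics overlap.** Controls are also taught about diet, exercise, weight, blood pressure and lipids. This probably makes the manual's added effect smaller. But the talk is given once and orally, and the intervention arm gets the manual in addition to it.

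**The package is disclosed.** The strengths paragraph of the Discussion does name health education together with breathing exercise. That makes the inconsistency plainer: one section describes a package, while the objective and the arm summary describe a single component.

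**This is a condensed article.** The point rests on what is stated. The manual is assigned explicitly to the intervention arm, as a measure on top of routine education.

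**Stronger readings that a reader might infer are not supported.** One could treat every intervention contact as a home visit and report a many-fold gap in contact time, but no split is given. One could add the three classroom days to the extra contact, but they teach and correct the breathing technique and so belong to VBE. One could express the manual's contribution as a share of the 0.447 target effect size, but nothing in the article says how large that contribution is.

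**Conclusion.** The point holds in this form: the trial as described can estimate the effect of VBE together with a manual and denser follow-up, but cannot attribute a difference to breathing exercises alone. The effect of the whole package remains estimable, so the comparison is not invalid; the question and the comparison do not match.

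The scheduled contact difference is 6 to 3 if the Control group section is complete, and smaller if Table 1 applies to both arms. The documents do not allow the effect of the manual or of the contacts on HRV or RPP to be sized. That the manual covers diet, exercise, heart rate and blood pressure is inferred from its search terms, since its content is not given.

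**What to change.** 1. **Manual.** Give the same SCAD education manual to both arms at enrolment. Cost: about 70 more copies. It would also take the manual out of the Step 2 before–after contrast. Report that the 16 patients already recruited were under the old plan.
2. **Assessment visits.** Reconcile Table 1 and Primary outcome measure with the Control group section, so that both arms attend the same assessment visits, with RPP at weeks 2, 8 and 12 in the outpatient classroom. If Table 1 already covers controls, this is a clarification at no cost. If not, and taking week 12 as attended in any case for close-out, RPP at weeks 2 and 8 adds 2 × 70 = 140 control attendances; weeks 1, 3 and 4, for vital signs and weight, add 3 × 70 = 210.
3. **Wording.** The denser follow-up and home visits may stay unmatched as support for VBE. In that case, state the objective and conclusion as the effect of a VBE programme with its follow-up support. If the manual also stays in one arm, state them as the effect of VBE plus education and follow-up, and list this among the limitations. This costs only redrafting.

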#### Control group

Routine education: on the first day after enrollment, researchers explain relevant knowledge of SCAD to patients, including risk factors, diet, weight control, physical exercise, blood pressure, lipid management, etc.Telephone follow-up: once per month for 3 months, each call lasting about 5–10 min, receiving telephone counseling from patients.Post-intervention: the control group will be given the same intervention measures 3 months later, and the effects of the control group will be compared before and after the intervention.

### Outcome

#### Primary outcome measure

The change in the HRV and RPP will be used as the primary outcome measure. The mean difference between the change scores of the two groups will be calculated.
HRV: currently, a 24-h time-domain analysis index is generally recommended for HRV detection [35]. All patients will be tested by 12-channel dynamic ECG (TLC5000) to detect the time-domain index of HRV between visit 1 (baseline) and visit 8 (after treatment). During the examination, participants are required to have adequate sleep overnight, maintain a quiet and peaceful environment, avoid extremely intense exercise, avoid changes in posture and mood swings, avoid drinking stimulating drinks such as coffee, and try not to take drugs that may interfere with autonomic nerves.

Indicators include: (1) standard deviation of normal-to-normal (SDNN), SDNN is the SD of 24 h continuous RR interval; (2) SD of average 5-min normal-to-normal intervals (SDANN), SDANN is the SD of the mean of continuous RR intervals every 5 min for 24 h; (3) square root of the mean squared differences of successive normal-to-normal intervals (RMSSD), RMSSD is the root mean square of all RR intervals within 24 h; (4) percent of the number whose difference between adjacent normal-to-normal intervals are > 50 ms (PNN50), PNN50 is the percentage of sinus beats in which the difference between the two adjacent normal RR stages was > 50 ms at 24 h; (5) mean of SDs of normal-to-normal intervals for each 5-min period (SDNNindex), SDNNindex is the mean of the SDs for 5-min segments.

All dynamic electrocardiograms are completed by professionals in the electrocardiogram room of the same hospital; HRV time-domain indexes are automatically analyzed and calculated by the electronic computer.
2.RPP: RPP is used to estimate myocardial oxygen consumption [36]. The normal value of RPP is < 12,000, and the smaller the product, the more stable the patient’s condition. In this study, an electronic blood pressure monitor (OMRON, HEM-4011C) will be used to measure patients’ heart rate and blood pressure at visits 1, 4, 7, and 8. The measurement time is scheduled to be from 14:002 to 15:00 and the room temperature is maintained at about 25 °C in the same outpatient classroom. After sitting for 15 min, the patient will be measured at the right elbow. Patients should ensure that they do not eat or drink strong tea, coffee, or other stimulating drinks 1 h before the measurement.

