### Statistical analysis

The Kolmogorov–Smirnov test and p-p diagram analysis will be used to test the normal distribution of continuous variables. Continuous variables will be presented by mean ± SD if they are normally distributed. Mann–Whitney U test will be used and expressed by median with interquartile range if they are not normally distributed. Chi-square or Fisher’s exact tests will be used for comparison of dichotomous data. Both per-protocol (PP) and ITT analyses will be used to determine the robustness of the evidence. An independent statistics expert will perform the statistical analysis in a blind manner. All statistical analyses of the data will be performed by using SPSS software version 21.0 (SPSS Inc., Chicago, IL, USA). A multivariate analysis will be performed to identify the factors associated with outcome indicators. Statistical significance is obtained with a *P* value < 0.05.

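### The primary outcome is five HRV indices plus RPP with no primary index, RPP visit or success rule, so the 5% significance level holds only under a rule the plan does not state

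*Protocol article*

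**What the plan says.** Under Objectives, the aim joins two domains: "The main goal of this RCT is to evaluate the effect of VBE on HRV and myocardial oxygen consumption in patients with SCAD". The Primary outcome measure section carries this over ("The change in the HRV and RPP will be used as the primary outcome measure") and defines the contrast: "The mean difference between the change scores of the two groups will be calculated".

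The same section then sets out the variables:

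- **HRV.** The recording is used to "detect the time-domain index of HRV between visit 1 (baseline) and visit 8 (after treatment"). The wording is singular, but a list of five follows, opening with "Indicators include: (1) standard deviation of normal-to-normal (SDNN") and continuing with SDANN, RMSSD, PNN50 and SDNNindex. None is marked as the primary one.
- **RPP.** The device will "measure patients’ heart rate and blood pressure at visits 1, 4, 7, and 8". By Table 1 the three post-baseline visits are weeks 2, 8 and 12. None is marked as primary.

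The Statistical analysis section gives one criterion: "Statistical significance is obtained with a *P* value < 0.05". The Sample size section uses one effect size (0.447) at a 5% significance level for superiority on HRV and myocardial oxygen consumption, and does not say which variable the effect size describes.

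**The concern.** A primary outcome has to fix which variable, at which time, decides the trial. Here the reader can identify two domains but not the deciding test. Six change scores to week 12 qualify as they stand (five HRV indices and RPP), and two more would qualify if the earlier RPP visits were treated the same way.

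The research hypothesis makes a claim on a single index plausible. It speaks of raising vagal and/or lowering sympathetic activity, and the Discussion links RMSSD mainly to vagal tone, SDANN mainly to sympathetic tone and SDNN to the overall level. A significant result on any one of these could be presented as confirming the hypothesis, and nothing in the document prevents the choice being made after the data are seen. A primary claim reached that way would not carry the 5% error rate used to size the trial.

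**Working it through.** **Inputs from the protocol article.** Five HRV indices, each with one change score (visit 1 to visit 8). RPP at one (visit 8) or three (visits 4, 7, 8) post-baseline visits. Threshold 0.05, taken here as two-sided because the article does not say. No familywise error rate is stated, so the only figure to compare with is the 5% level in the Sample size section.

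**Inputs assumed.** The correlations between test statistics are not in the document, so a range is shown. The calculation supposes no true effect and counts a false positive when at least one test is significant.

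**Step 1: independent tests.** Chance of at least one false positive = 1 − 0.95^m.

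- m = 2 (one HRV index, RPP at one visit): 1 − 0.9025 = 9.75%
- m = 6 (five HRV indices, RPP at week 12): 1 − 0.7351 = 26.5%
- m = 8 (five HRV indices, RPP at weeks 2, 8 and 12): 1 − 0.6634 = 33.7%

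**Step 2: correlated tests.** Multivariate normal simulation, 1,000,000 draws per setting, with the same correlation between all tests:

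| Common correlation | Six tests | Eight tests |
|---|---|---|
| 0.3 | 24.2% | 29.9% |
| 0.5 | 20.7% | 24.9% |
| 0.7 | 16.4% | 19.0% |
| 0.8 | 13.9% | 15.7% |
| 0.9 | 10.8% | 12.0% |

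A common correlation also ties HRV strongly to RPP. If HRV and RPP are instead correlated only 0.1, six tests give 24.7% at a between-index correlation of 0.3, 17.0% at 0.8 and 14.6% at 0.9. Across both structures the six-test range is about 11-25%.

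**Step 3: the smallest version of the problem.** With one HRV index and one RPP visit, either sufficient, the result is 9.75% if independent and 9.1% at correlation 0.5.

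**Step 4: the opposite rule.** If one named HRV index and RPP at one named visit must both be significant, the false positive rate is at most 5%. The cost moves to power: two endpoints with 80% each give 0.8 × 0.8 = 64% joint power if independent, more if positively correlated.

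**The case against.** The strongest reply has four parts.

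1. **No any-one-wins rule is stated.** The Statistical analysis section gives a significance threshold, not a success criterion, and the Sample size section words the hypothesis with an "and". If that means both domains must succeed, with one variable and visit each, there is no inflation. This stands: the inflation figures are conditional. It does not rescue the plan, because that rule is not stated either, and it would still need one HRV index to be chosen.
2. **Three RPP tests are an inference.** A reader might infer eight primary tests from "heart rate and blood pressure at visits 1, 4, 7, and 8", but that is a measurement schedule. HRV change runs to visit 8, visit 8 is close-out, and the randomised comparison lasts three months, so week-12 RPP is the natural reading. This stands, and six is the count to lead with.
3. **Independence is implausible.** Five indices from one recording are correlated, and the Discussion itself says that PNN50 moves much as RMSSD does. This stands, so 26% is a ceiling for six tests and the correlated range is the more realistic one.
4. **Multiplicity adjustment may sit in an analysis plan that is not shown, and this is a condensed article.** This stands for the adjustment, whose absence alone would be no finding. It does not stand for the primary variable and visit, which this section exists to define. The article describes every index in detail, so condensation does not explain the missing choice.

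The trial is also presented as a step towards larger ones, with all indices disclosed. That lessens the harm but does not supply a defined primary test.

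**Conclusion.** The point holds in conditional form. The primary outcome names no HRV index, no RPP visit and no success rule, and pairs this with an unadjusted 0.05. If any one of six week-12 results sufficed, the false positive chance would be at most about 26%, and roughly 11-25% under assumed correlations of 0.9 to 0.3. With just one index and one RPP visit, either sufficient, it is about 9-10%.

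A reader might infer that the trial's error rate simply is 17-34%. The document does not support that. The 34% end needs eight primary tests, full independence and an any-one rule. The 17% end is no floor, because it depends on where the assumed correlation stops, and stronger correlation brings six tests to about 11%. What the document does support is narrower: the stated 5% level is guaranteed only under a rule that the plan leaves out.

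**What to change.** By a dated protocol and registry amendment, made before any outcome data are examined:

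- Name one HRV index as primary. 24-h SDNN is a reasonable candidate because the Discussion says it reflects overall HRV; the Objectives themselves name no index.
- Name RPP as the other primary variable. Define both as change from baseline to visit 8 (week 12).
- State one rule that controls the 5% level. One option is fixed order, SDNN then RPP, each at two-sided 0.05, which follows the order of domains in the Objectives. Requiring both, or splitting alpha (for example 0.025 each), would be equally valid.
- Make the other four HRV indices and RPP at visits 4 and 7 secondary, without confirmatory claims.
- Say which variable the 0.447 effect size belongs to, so that power under the chosen rule can be checked.

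**Cost.** No change to visits, measurements or recruitment. It is, however, a change to the primary outcome with 16 patients already recruited (Trial status), which is why the date and the state of data access should be recorded. Under fixed order, RPP cannot be claimed as confirmatory if SDNN is not significant. A both-must-succeed rule lowers joint power, and a split alpha lowers power for each variable. The remaining indices lose primary status in every case.

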### Sample size

The sample size estimation was carried out using G Power 3.1.9.2 software of two population means formulae [31]. We hypothesized that the VBE-based clinical trial monitoring group would be superior to the control group in terms of HRV and myocardial oxygen consumption; the effect rates were calculated with a 0.447 effect size at a 5% significance level and a power of 0.8. This means a sample size of 118 individuals per group was required. With an estimated 20% dropout, the final sample size of 140 individuals was determined (70 in each group).

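### The primary comparison of HRV and RPP is an unadjusted difference in change scores; adjusting for the baseline already measured would be more precise at no cost

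*Protocol article*

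**What the plan says.** Under Primary outcome measure, the protocol article defines the endpoint as a change: "The change in the HRV and RPP will be used as the primary outcome measure". It then fixes the contrast: "The mean difference between the change scores of the two groups will be calculated".

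Both outcomes have a baseline value. Dynamic ECG is used "to detect the time-domain index of HRV between visit 1 (baseline) and visit 8 (after treatment"), and an electronic monitor is used to "measure patients’ heart rate and blood pressure at visits 1, 4, 7, and 8". Table 1 marks both HRV and RPP at the screening visit and at week 12.

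The Statistical analysis section names no baseline covariate for the comparison of the arms. It begins with a distribution check: "The Kolmogorov–Smirnov test and p-p diagram analysis will be used to test the normal distribution of continuous variables". For data that fail it, "Mann–Whitney U test will be used and expressed by median with interquartile range if they are not normally distributed". The only model mentioned has another purpose: "A multivariate analysis will be performed to identify the factors associated with outcome indicators".

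The Sample size section states that "the effect rates were calculated with a 0.447 effect size at a 5% significance level and a power of 0.8". It does not say which standard deviation the effect size refers to, and the article gives no SD or baseline-to-follow-up correlation.

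**The concern.** A change score uses the baseline, but with its coefficient fixed at 1. ANCOVA estimates that coefficient from the data. Unless the true slope of the week-12 value on baseline is 1, subtracting the whole baseline over-corrects or under-corrects and leaves avoidable variance in the treatment contrast.

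This is a stated choice and not a detail left open, because the outcome section names the contrast for the primary outcomes. At stake is precision: wider confidence intervals and lower power than the same patients and measurements could give. A smaller point concerns the effect measure. The outcome section promises a mean difference, while the analysis section provides a rank test with medians for non-normal variables. If that switch were applied to a primary outcome, the headline effect measure would depend on a test run on the trial data.

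**Working it through.** **Inputs from the article**
- 70 per arm and 20% dropout (Sample size), so 70 × 0.8 = 56 evaluable per arm.
- Effect size 0.447, 5% significance level (Sample size). Sidedness is not stated; two-sided is used here.

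**Assumptions, not in the article**
- Equal variance s² at baseline and week 12.
- Baseline-to-week-12 correlation r between 0.3 and 0.9.
- For power only: 0.447 is expressed in SDs of the change score.

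**The plan's own figure.** The article gives no figure for the precision of the primary contrast, so there is none to reproduce. Its sample size (118 per group, then 140 in total) does not follow from 0.447, 5% and 80%: the two-sided normal formula gives 79 per arm and the one-sided formula 62. That is a separate matter and no part of the evidence here.

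**Variance comparison**
- Change score: Var = 2s²(1 − r) per patient.
- ANCOVA: Var = s²(1 − r²) per patient.
- Ratio ANCOVA/change = (1 − r²) / [2(1 − r)] = (1 + r)/2.
- Extra patients needed by the change score = 2/(1 + r) − 1.

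Without the equal-variance assumption, the change-score variance exceeds the ANCOVA variance by Var(baseline) × (1 − slope)². This is never negative, so in large samples ANCOVA is never the less precise of the two. Estimating the slope costs one degree of freedom, which is negligible at this size.

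**Power at 56 per arm** (noncentral t, two-sided). The effective standardised effect is 0.447/√[(1 + r)/2] and the noncentrality is that value × √(56/2). For the change score itself, the noncentrality is 0.447 × 5.292 = 2.365 and power is 65%.

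| Assumed r | Variance ratio (1 + r)/2 | Extra patients for change score | Effective effect size, ANCOVA | Power, ANCOVA (change score: 65%) |
|---|---|---|---|---|
| 0.3 | 0.65 | 54% | 0.554 | 83% |
| 0.5 | 0.75 | 33% | 0.516 | 77% |
| 0.7 | 0.85 | 18% | 0.485 | 72% |
| 0.8 | 0.90 | 11% | 0.471 | 70% |
| 0.9 | 0.95 | 5% | 0.459 | 67% |

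A simulation of 20,000 trials with 70 per arm gave change-to-ANCOVA variance ratios of 1.539 at r = 0.3 and 1.175 at r = 0.7. The formula 2/(1 + r) gives 1.538 and 1.176.

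**Does the normality check itself cost anything?** Log-normal data were simulated with log-SD 0.4, an effect of 0.447 SD on the log scale, 56 per arm and 2,000 runs per setting. Power for r = 0.3/0.5/0.7 was:
- test chosen by the normality check: 51/64/85%
- t-test on the raw change in every run: 51/64/85%
- Mann–Whitney on the change in every run: 51/64/85%
- ANCOVA on the raw scale: 65/73/88%
- ANCOVA on the log scale: 69/77/92%

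The type I error of the switched procedure was 0.050 to 0.053. The switch therefore costs essentially no power or error control in this setting. Nearly all of the gain comes from the baseline covariate. The further 3 to 4 points from the log scale reflect an assumed model that suits it.

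**The case against.** The strongest reply is that nothing here is an error. A comparison of mean changes is a recognised analysis that holds its 5% level and is unbiased under randomisation. Preferring ANCOVA is advice about efficiency, and the size of the benefit rests on a correlation that the article does not report. At r of 0.8 to 0.9 the gain is only 5 to 11% in patients and 2 to 5 points of power. The power figures also need 0.447 to be in change-score SDs, which the article does not say. All of this stands, and it makes the point a recommendation with an assumed range.

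Three stronger readings are tempting, and the documents do not support them.

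- **Bias from chance imbalance.** A reader might infer that leaving out the baseline covariate biases the result when the arms differ at baseline by chance. Under randomisation, that imbalance is part of the variance of an unbiased contrast. It is already counted in the ratios above and must not be counted again.
- **Harm from the normality check.** A reader might infer that switching tests damages the primary analysis. The Statistical analysis section applies the check to continuous variables in general and does not tie it to the primary change scores. The simulation also shows no material loss. What remains is that a rank test does not estimate the mean difference promised in the outcome section.
- **Visit-by-visit testing of RPP.** A reader might infer that RPP is tested one visit at a time and that patients with a missing visit are dropped. The article says neither. It says that withdrawn patients are followed up for outcomes and that intention-to-treat is used; further detail may lie in an analysis plan.

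The planned multivariate analysis does not answer the point, because its stated aim is to find factors associated with the outcomes, not to compare the arms.

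**Conclusion.** The point holds as a free improvement. The article commits the primary comparison to an unadjusted difference in change scores although the baseline of each primary outcome is measured. In large samples that contrast is never more precise than ANCOVA, and it is less precise whenever the slope on baseline differs from 1.

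The size cannot be fixed from the article. The table's range of 5% to 54% extra patients, and power of 67% to 83% against 65%, is conditional on the assumed r, equal variances and, for power, the assumed scale of 0.447. No single figure should be quoted as a property of this trial. The planned contrast is neither invalid nor biased.

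**What to change.** State that the primary treatment comparison, for each HRV index and for RPP at week 12, is an ANCOVA with arm and the baseline value of that outcome as terms. Decide in advance, before outcome data are seen, which clearly skewed indices are analysed on the log scale. Report the adjusted difference (or, on the log scale, the adjusted ratio) with a 95% confidence interval.

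Keep the change-score or Mann–Whitney comparison as a sensitivity analysis, so that the primary effect measure does not depend on the Kolmogorov–Smirnov result.

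The cost is analysis wording only: no new visits, measurements or patients. The Trial status section reports 16 patients recruited at the time of writing, so at that stage the change could still be specified before any outcome analysis.
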